### Assignment of interventions: blinding

This study is an open-label trial, where both the researchers and participants are aware of the treatment or medication they are receiving. The radiologists who assess the MRI results are blinded to the patient assignment group and clinical information.

### Data collection and management

#### Data management

Investigators will enter the data required by the protocol into the case report forms (CRF). The principal investigator is responsible for assuring that data entered into the CRF is complete and accurate, and that entry is performed in a timely manner. The signature of the investigator will attest to the accuracy of the data on each CRF. All data management activities will be completed prior to the final closure of the database.

#### Confidentiality

All patient data collected and processed for the purposes of this study will be managed by the investigators with adequate precautions to ensure the confidentiality of the data and in accordance with applicable national laws and regulations on personal data protection. No patient-identifiable data will be obtained. In any presentation of the results of this study, at meetings, or in publications, the patients’ identities will remain confidential. In all activities, the General Data Protection Regulation will be followed to ensure the protection of sensitive personal information, and the study will be performed in accordance with the World Health Organization guidelines for good clinical practice.

#### Plans for collection, laboratory evaluation, and storage of biological specimens for genetic or molecular analysis in this trial/future use

The collected samples will be stored at Ewha Womans University Mokdong Hospital and sent to an analytical institution for analysis after the intervention and maintenance period is completed.

## Statistical methods

### Statistical methods for primary and secondary outcomes

Descriptive statistics will be computed for all variables: mean and standard deviation for continuous variables, unless stated otherwise, and frequency and percentage for categorical variables. Intention-to-treat will be performed mostly. Comparisons will be made within groups (post- vs. pre-intervention for each group) and between groups (ICR vs. SOC). Independent and paired *t*-tests will be used to compare continuous variables between and within groups, respectively. To estimate the pre/post-values and changes within and between the diets for the primary and secondary outcomes, a linear mixed model will be used. SPSS version 23 (SPSS Inc., Chicago, USA) will be used for statistical analysis. All two-sided *P* value < 0.05 will be considered as statistically significant.

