**Methods:**

We will include adult (19–75 years) NAFLD patients. NAFLD will be diagnosed by histologic assessment or magnetic resonance imaging-proton density fat fraction (MRI-PDFF) ≥ 8%. A total of 72 patients will be classified according to BMI (obese group: BMI ≥ 25 kg/m^2^ [*n* = 36] and non-obese group: BMI < 25 kg/m^2^ [*n* = 36]). Participants will be followed up for 24 weeks. Participants will be randomly assigned to one of the two groups: the SOC or ICR group. The primary objective will be the change in liver fat content measured using MRI-PDFF from baseline to 12 weeks.

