### Outcomes

The primary objective is to evaluate the impact of ICR on liver steatosis measured using MRI-PDFF (time frame: baseline and 12 weeks), and the outcome of interest is a change in the MRI-PDFF value of at least 30% with ICR. Secondary objectives include changes in liver fibrosis by MRE (time frame: baseline and 12 weeks); anthropometrics including BMI (kg/m^2^) (time frame: baseline, 12 and 24 weeks); BCA measured using InBody (time frame: baseline, 12 and 24 weeks); VAT measured using fat computed tomography (CT) (time frame: baseline, 12 and 24 weeks); QOL score measured using Chronic Liver Disease-NAFLD Questionnaire (CLDQ) (time frame: baseline, 12 and 24 weeks); hormones including leptin, adiponectin, ghrelin, GLP-1, apelin, chimerin, and osteopontin (time frame: baseline and 12 weeks); liver metabolites including diglycerides, fatty acid, phosphatidylethanolamines, phosphatidylcholines, methionine, S-adenosyl-l-methionine, and methylthioadenosine (time frame: baseline and 12 weeks); and gut microbiota analyzed with 16S rRNA gene sequencing (time frame: baseline and 12 weeks). Polymorphisms of PNPLA3, TM6SF2, TM4SF5, SREBF2, MBOAT7-TMC4, HSD17B13, and adenine insertion (A-INS) will also be analyzed using next-generation sequencing (NGS). The objectives of this study are summarized in Table 1.

**Table 1 Tab1:** Objectives of the Nonalcoholic Fatty Liver Disease-Intermittent Calorie Restriction (FLICR) study

	Study time points (weeks)			
	Intervention period			Maintenance period
	0	6	12	24

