### Sample size

In a previous study, the percentage of participants who reached the endpoint of a relative reduction in liver fat content > 30% measured using MRI-PDFF after 12 weeks was 80% in the ICR group and 29% in the control group [17]. Based on this assumption, 72 participants (36 in the obese group and 36 in the non-obese group) are planned to be randomized into the two treatment groups in a 1:1 ratio (ICR:SOC) to achieve 80% power for superiority comparison (Fisher’s exact test) of the primary objective between the two treatment groups, with a two-sided type I error of 5% and allowing for a 10% dropout rate. G*Power 3.1.9.4 was used to calculate the sample size.

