### Assignment of interventions: allocation

For eligible patients, the principal or sub-investigator will complete the patient enrollment form and enroll the patients. Patients will be randomly assigned to receive ICR or SOC by the enrolling investigator via a computer-generated randomization sequence using block randomization (block size = 6) with a 1:1 ratio and stratification by BMI (≥ 25 and < 25 kg/m^2^). After the participants have been assigned to the ICR or SOC group through the randomization procedure, they will be informed by the enrolling investigator.

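### A t-test and a linear mixed model are both planned for the same between-arm comparisons, with no statement of which decides and no stated adjustment for BMI stratum or baseline value

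*Protocol article*

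**What the plan says.** All references are to the protocol article.

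- **Statistical methods for primary and secondary outcomes.** Independent and paired "tests will be used to compare continuous variables between and within groups, respectively". No covariate is named. The next sentence says that, to estimate values before and after and "changes within and between the diets for the primary and secondary outcomes, a linear mixed model will be used". Its terms are not listed, and the section does not say whether the t-test or the model is the deciding analysis.
- **Assignment of interventions: allocation.** Allocation uses "block randomization (block size = 6) with a 1:1 ratio and stratification by BMI", cut at 25 kg/m². The plan is 36 patients per stratum.
- **Methods for additional analyses.** BMI group returns only here, as a subgroup analysis.
- **Primary outcome.** The abstract gives it as "change in liver fat content measured using MRI-PDFF from baseline to 12 weeks". The Outcomes section adds that "the outcome of interest is a change in the MRI-PDFF value of at least 30% with ICR". Tables 1 and 2 place MRI-PDFF at weeks 0 and 12 only.
- **Sample size.** The trial is sized on the responder form with an unstratified Fisher's exact test "to achieve 80% power for superiority comparison", from an earlier study in which the responder rate "was 80% in the ICR group and 29% in the control group". The statistical methods section does not name that test.

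**The concern.** Two things are at stake.

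First, two methods are named for the same comparison without a ranking. Depending on its terms, the mixed model can give a different estimate and p-value from the t-test. In an open-label trial this leaves room to choose between them after the data are seen.

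Second, the one between-arm test that is fully specified for continuous outcomes leaves out two variables that are free to use: the factor on which randomisation was stratified, and the baseline value. When a stratification factor is prognostic, an analysis without it leaves between-stratum variance in the error term, although the design has already removed that variance from the arm difference. When the baseline is correlated with the follow-up, an unadjusted comparison gives up precision and carries chance baseline imbalance into the estimate. With about 32 evaluable patients per arm, the baseline difference between arms has a standard error of sqrt(2/32) = 0.25 SD, so some imbalance is to be expected.

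**Working it through.** **The plan's own figure.** With 80% versus 29%, two-sided Fisher at 5%, exact enumeration gives 76.1% power at 16 per arm and 81.1% at 17 per arm. Then 34/0.9 = 37.8, so 38 patients, against the stated 36 per BMI group. With 16 and 17 evaluable patients in the two arms, power is 83% to 84%, and 33/0.9 = 36.7, so 37. The stated figure is therefore reproduced to within 2 patients if the calculation was done per BMI group. For the pooled comparison, 72 × 0.9 = 64.8, about 32 per arm, and power is 98.6%.

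**Assumed inputs.** The documents give no SD for PDFF, no baseline to week-12 correlation (rho) and no difference in PDFF change between BMI strata (d). I take rho = 0.3, 0.5, 0.7 and d = 0, 0.5, 1. Units are the within-stratum SD, equal at both visits. There are 72 patients and no dropout.

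**Effect of leaving out the stratum.** Each stratum of 36 is 6 full blocks of 6, so it splits 18/18 and the stratum effect cancels from the arm difference. The within-stratum variance of change is 2(1 − rho).

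- True variance of the arm difference: (4/72) × 2(1 − rho).
- Variance reported by the t-test: (4/72) × [2(1 − rho) + d²/4], approximately.

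At rho = 0.5 the true SE is sqrt(0.0556 × 1) = 0.236. The reported SE is sqrt(0.0556 × 1.0625) = 0.243 at d = 0.5 and sqrt(0.0556 × 1.25) = 0.264 at d = 1. Simulation of the stratified blocks (4000 trials per scenario) agrees: reported against empirical SE is 0.235 vs 0.239 (d = 0), 0.242 vs 0.236 (d = 0.5) and 0.263 vs 0.239 (d = 1).

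Simulated type I error of the t-test on change (Monte Carlo error about 0.3 points):

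| rho | d = 0 | d = 0.5 | d = 1 |
|---|---|---|---|
| 0.3 | 5.2% | 4.8% | 3.3% |
| 0.5 | 5.1% | 4.5% | 2.8% |
| 0.7 | 5.1% | 4.1% | 1.9% |

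The stratum-adjusted test stays between 4.9% and 5.3% throughout.

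**Effect of leaving out the baseline.** With equal variances, ANCOVA variance relative to the change-score t-test is (1 − rho²)/[2(1 − rho)] = (1 + rho)/2. This gives 0.65, 0.75 and 0.85. The inverses, 1.54, 1.33 and 1.18, mean that the t-test would need about 54%, 33% and 18% more patients for the same precision. Relative to a t-test on raw week-12 values the ratio is 1 − rho²: 0.91, 0.75 and 0.51.

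**Power, true effect 0.6 SD:**

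| rho | d | t-test on change | with stratum | with stratum and baseline |
|---|---|---|---|---|
| 0.3 | 0.5 | 55.9% | 57.8% | 74.4% |
| 0.5 | 0.5 | 69.0% | 71.4% | 83.1% |
| 0.7 | 0.5 | 88.0% | 90.0% | 93.8% |
| 0.3 | 1 | 49.5% | 56.5% | 74.6% |
| 0.5 | 1 | 62.7% | 70.9% | 82.5% |
| 0.7 | 1 | 81.0% | 89.8% | 93.4% |

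The stratum alone adds about 2 points at d = 0.5 and 7 to 9 at d = 1. The baseline adds more in every row except the last.

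**Does the mixed model already solve it?** With PDFF at two visits and complete data, a model with free arm-by-time means reproduces the change-score t-test. In three simulated datasets its SEs were 0.282, 0.225 and 0.233, equal to the t-test's. A model that constrains the arms to a common baseline mean gave 0.236, 0.197 and 0.208, against 0.241, 0.214 and 0.223 for ANCOVA on baseline. The gain therefore depends on terms that the article does not state.

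**The case against.** The best defence is that the article is a condensed account. It does name a mixed model of values before and after, which uses the baseline data, and the fixed effects of such a model are normally listed in the full protocol or SAP, neither of which is shown. This stands to a point. A reader might infer that every between-arm comparison is an unadjusted t-test and that baseline PDFF is ignored; the documents do not establish that. Unlisted terms are not excluded terms. What remains is that the article does fix an independent t-test for between-arm comparison and does not rank it against the model.

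A reader might also infer that the standard-error mismatch threatens validity. It does not. It arises only if BMI stratum predicts PDFF change, which no section shows. It always runs in the conservative direction and does not bias the estimate.

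A third inference would be that the loss is worst within the BMI subgroups of about 16 evaluable patients per arm. Within a subgroup the BMI group is constant, so leaving it out costs nothing there, and the ratio (1 + rho)/2 does not improve as the sample shrinks.

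Finally, the variance ratios concern baseline adjustment of a continuous outcome. They do not carry over to the responder outcome, for which pooled power is already 98.6% at the planning rates.

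**Conclusion.** The point holds as a free improvement that should be made. It is not a flaw that invalidates the trial. The article names two between-arm methods for the same outcomes without saying which decides, and states neither stratum nor baseline adjustment for either.

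The cost of omitting the stratum ranges from nothing, if BMI is not prognostic, to a type I error of 2.8% in place of 5% at d = 1 and rho = 0.5. The cost of omitting the baseline is a variance that could be cut to 0.65 to 0.85 of the change-score value. Both sizes rest on assumed rho and d and on equal variances at the two visits. The power figures also assume an effect of 0.6 SD and no dropout. If the full protocol or SAP already designates a model with these terms, what is left is to bring the article's wording into line with it.

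**What to change.** - **Continuous outcomes.** State one deciding between-arm analysis per outcome: a linear model of the week-12 value with arm, baseline value and BMI stratum, or a mixed model with the same terms where week 24 is also measured. Report the adjusted difference with its 95% CI. Keep the independent and paired t-tests as description only.
- **Responder outcome (30% PDFF reduction).** Name one BMI-stratified analysis, for example a Cochran-Mantel-Haenszel test stratified by BMI, in place of the unstratified Fisher's exact test.
- **Timing.** Trial status says that recruitment closed in January 2023, so date the statement and settle it before outcomes are examined by arm.

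The cost is wording and minor analysis work. BMI stratum and baseline values are already collected, the planned software fits these models, and no change to sample size or visits is needed.

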### Interim analyses

We will not perform interim analysis to preserve statistical power and data integrity and to minimize bias and data-dependent decisions. If significant harm or safety issues arise during the trial, the study may be halted to protect the participants. The study will be also stopped if ethical concerns, such as the emergence of a new standard of care, develop.

### Methods for additional analyses (e.g., subgroup analyses)

Subgroup analyses will be performed according to the obese and non-obese groups.

### Methods in analysis to handle protocol non-adherence and any statistical methods to handle missing data

The main analyses will be performed based on the intention-to-treat population, and missing data will be assumed to be missing at random.

### Plans to give access to the full protocol, participant-level data, and statistical code

The datasets analyzed during the current study and statistical code are available from the corresponding author upon reasonable request, as is the full protocol.

### Oversight and monitoring

#### Composition of the coordinating center and trial steering committee

There will always be a group running the trial day-to-day and providing organizational support and knowing how often they will meet, plus information on other committees providing oversight such as a Trial Steering Committee.

#### Composition of the data monitoring committee, its role, and reporting structure

An independent data monitoring committee will be established with two individuals from the Department of Biostatistics, Ewha Womans University Mokdong Hospital. The management team will observe the progress and data monthly by mail and web conferencing. If the monitoring committee decides that on-site monitoring is necessary, members will visit the site for face-to-face monitoring.

#### Adverse event reporting and harms

All AEs during the study will be recorded with the following data: date of onset and date of completion (if applicable), severity of AEs, investigator’s view on the relationship to dietary intervention, taken actions on AEs, treatment of the AEs, cause of the event (if known), and outcome. The AE intensities will be graded according to the National Cancer Institute’s Adverse Event Common Terminology version 4.03.

#### Frequency and plans for auditing trial conduct

The project management group will meet to review trial conduct every month, and the trial steering group and the independent data monitoring and ethics committee will meet to review the trial conduct every 3 months throughout the trial period.

## Discussion

NASH can progress to cirrhosis, HCC, and death and is an increasing indication for liver transplantation [4]. Because of the lack of effective pharmacological therapies, lifestyle modifications are the mainstay of treatment for NAFLD [5]. Although no obvious effect of specific dietary therapies has been observed in previous studies, reduced energy intake resulted in weight loss, decreased intrahepatic fat content, decreased liver enzyme levels, and decreased insulin resistance in several RCTs [8, 9, 18]. Therefore, the current recommendations are limited to the restriction of total daily calorie intake within 1500–1800 kcal in men and 1200–1500 kcal in women or a reduction in total energy intake of > 500 kcal/day [19].

ICR, as a novel dietary approach in the treatment of NAFLD, has the two most common strategies of strict alternate-day fasting and a 5:2 diet with two self-selected days with extreme energy restriction and 5 days without calorie restriction [13, 20]. Recent studies have demonstrated a greater reduction in liver steatosis with ICR than that with SOC in NAFLD patients [13, 15, 16]. Other studies suggested that insulin concentrations and fat mass were significantly reduced with ICR compared to that with CCR, with similar amounts of net calorie intake and weight loss [14, 15]. ICR can also improve dietary compliance and reduce cardiometabolic risks [17, 20]. However, only few studies have assessed liver fat content with MRI to date [17]. In addition, active calorie restriction according to the guidelines was not performed in the control group [17].

Despite these promising findings, further studies are required to address the multiple areas of uncertainty. It remains to be elucidated whether ICR is superior to CCR at similar amounts of net energy intake with respect to a broader set of metabolic health indicators [7]. In addition, analyses of long-term maintenance of initial weight loss and metabolic outcomes with ICR are required to investigate its sustainability and practicability [8, 9] because the first systematic review of the few ICR studies that had longer than 6 months of follow-up did not show greater benefits of ICR compared with those of CCR [18].


## Trial status

Recruitment of participants has begun in July 2022 and closed in January 2023.

## Data Availability

The datasets analyzed during the current study are available from the corresponding author on reasonable request, as is the full protocol.

## Abbreviations

NAFLD: Nonalcoholic fatty liver disease
NASH: Nonalcoholic steatohepatitis
HCC: Hepatocellular carcinoma
CVD: Cardiovascular disease
ICR: Intermittent calorie restriction
SOC: Standard of care
CCR: Continuous calorie restriction
BMI: Body mass index
MRI: Magnetic resonance imaging
PDFF: Proton density fat fraction
RCT: Randomized controlled trial
MRE: Magnetic resonance elastography
BCA: Body composition analysis
VAT: Visceral adipose tissue
QOL: Quality of life
FLICR: Fatty liver and intermittent calorie restriction
CT: Computed tomography
CLDQ: Chronic Liver Disease-NAFLD Questionnaire
NGS: Next-generation sequencing
AE: Adverse event
